# **EXECUTIVE SUMMARY**

Cervical cancer (CC) is almost entirely preventable with current technologies, yet, it remains the 4^th^ most common cause of cancer incidence and mortality among women globally.(1) CC is the most common cause of cancer and cancer deaths among women in Kenya, and 90% of CC deaths occur in low- and middle- income countries (LMIC).(2) To achieve the 2018 World Health Organization (WHO) call to action towards global CC elimination, there is an urgent need to adapt, implement, and scale-up effective technologies in LMICs.(3, 4)

The mainstay of CC prevention in LMIC has been the single-visit approach with screen-and-treat (SVA-SAT) method, using visual inspection with acetic acid (VIA) and ablative treatment with cryotherapy to manage precancerous lesions. It is a low-cost screening approach and minimizes loss to follow-up compared to traditional cytology.(5) Despite well-established evidence of the effectiveness of VIA on population-level reduction in CC burden,(6-8) the estimated screening uptake among women aged 30-49 in Kenya is 16%,(9) far below the WHO’s target of 70% and twice-lifetime screening of women ages 35-45 by 2030.(3) In Kenya, there is extremely low fidelity of SVA-SAT; up to 70% of screen-positive women do not receive treatment, demonstrating the science-practice gap.(10) The low treatment rate has been attributed to programmatic and logistical challenges of implementing cryotherapy in low-resource settings (e.g., equipment shortage, costs, supply chain difficulties of refrigerant gas, equipment failure, and treatment duration >10 min).(11-13) Thermal ablation (TA) is an effective alternative to cryotherapy for ablation of precancerous lesions, and has been recommended by the WHO since 2019.(14) Preliminary data from an investigative team member demonstrated safety, effectiveness, and acceptability to women when delivered by nurses in Zambia and Kenya.(15, 16) The portable device can be charged with electricity, batteries or solar panels, which is ideal for low-resource settings.(17) Successful implementation and scale-up of TA within the SVA-SAT approach could optimize CC prevention.

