**Table 3. Women screened for CC* in selected reproductive health facilities**

| **Facility** | **Women screened**  **(Jan-Apr 2020)** | **Screen positive** |
| --- | --- | --- |
| Kiambu level 4 hospital | 350 | 19 |
| Nyeri level 5 hospital | 206 | 8 |
| Thika level 5 hospital | 117 | 7 |
| Muranga level 5 | 45 | 4 |
| Coptic hospital (urban) | 74 | 8 |
| Karatina level 4 | 181 | 3 |
| Othaya level 4 | 91 | 10 |
| Kiandutu health center | 88 | 5 |
| Ngoliba health center | 10 | 2 |
| Ruiru level 4 | 75 | 4 |
| **Total** | **1237** | **70** |

Average of 300 screened per month and 5% positive

*Cervical cancer (CC)

**Justification for stepped wedge design**. Stepped wedge designs use sequential roll-out of an intervention (to individuals or clusters – in the present case, RH clinics) over time to assess the impact of an intervention, with the order of receiving the intervention determined at random.(56) The design is especially relevant for proven interventions that cannot be withheld ethically, but which cannot necessarily be moved to scale simultaneously in all the clinics with the resources at hand. All clusters are thus offered the intervention by the end of the study, with the order of initiation randomly assigned. Prior to a cluster offering the intervention, the cluster contributes data to the “pre-implementation” (e.g., control) period and once the cluster has begun to implement the intervention, it contributes to the “intervention” period.

This design allows for comparisons of key outcomes in the intervention versus control periods. SVA-SAT+TA is an ideal intervention candidate for a cluster**-**randomized stepped wedge design, given that it is

1) an evidence-based intervention

2) it is logistical and feasible to scale in a phased fashion (which then allows for assessment of implementation with each wave)

3) is implemented at the unit of the facility (i.e., thus we can randomize to phase of implementation at the clinic level).

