This design also allows us to quantify the effect of the intervention on screening coverage and treatment effectiveness, while providing data on background changes that might occur during the study period. Finally, this design allows for ample time to assess maintenance of the intervention following withdrawal of intensive study support. Assessing maintenance is critical for interventions introduced to public health facilities, where competing priorities, limited resources, and high patient-to-provider ratios may impede the sustainment of gains made during a study.

***Procedures and Implementation strategies****:* We will implement this work in 4 phases i.e., baseline data period, training phase, intensive implementation phase and maintenance phase.

***Baseline data period****:* We will obtain baseline data on facility-level infrastructure including availability of equipment, supplies, medications as well as current staffing (numbers, cadre and training) and patient flow. Routine data on the proportion of women screened, screened positive, and treated for abnormal lesions will be abstracted monthly, by research staff, for a minimum period of 6 months prior to introduction of the intervention starting with the first wave facilities (Fig**. 3).** During this period, all clinics will contribute data to the “control” arm.

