**Maintenance phase**

At the end of implementation for the last wave of clinics, all ten clinics will concurrently commence maintenance evaluation (Fig. 3). Technical support, however, will reduce after six months of intervention implementation. RH facilities will be assessed to determine their readiness for reduced technical assistance support using predefined metrics. Metric measures will include a review of number of providers trained and implementing SVA-SAT+TA, treatment completion rate, and experience of adverse events. The assessment will determine whether intervention implementation by facility personnel without the intervention of research personnel is maintained. Bi-annual facility level assessments will be done and they will include a review of infrastructure and staffing to see if there are changes in the preparedness across sites over the maintenance period*.*

**Outcome Variable:** Our primary study outcome is change in treatment completion rate among screen-positive women, comparing pre-and post-intervention periods. The impact of this work will be evaluated using the RE-AIM framework as follows (Table 4) :

- **REACH** refers to the number, proportion or representativeness of individuals or entities reached by an intervention. We will assess the number of providers trained within each clinic. If SVA-SAT + TA is adopted and implemented as intended, we expect the number of women receiving cervical cancer screening and treatment services to increase. We will abstract individual level program data and estimate the proportion of women aged 25-49 years seeking services in reproductive health clinics who are screened per month (target = 20%) and proportion of screen-positive women who complete treatment (target = 60%) comparing pre-implementation period to intervention periods. This will include women treated with cryotherapy, LEEP or any other procedure.

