**Power and sample size** According to data on cervical cancer screening and preventive treatment for Kiambu County from 2017-2019, 20% of cervical cancer screening clients who screened positive received cryotherapy or LEEP. Routine data from our proposed study facilities show an average of 30 clients per month were screened at each facility in the first three months of 2020 (**Table 3**), corresponding to approximately 10% of eligible clients. The primary effectiveness outcome is the proportion of screen-positive women who receive same day ablation treatment. Assuming six-month waves, 30 clients screened per month and a 5% screen positive rate, we will have an average of 9 screen-positive women per facility per wave. Assuming an intracluster correlation coefficient of 0.2, alpha=0.05 and 20% treatment coverage pre-intervention, we will have 80% power to detect a three-fold increase to 60% treatment coverage using thermal ablation (R (v 3.6.3) package swCRTDesign (v 3.1)). We estimate that 90% of screen positive women will be eligible for ablative treatment.(49)

**Data analysis**: The primary analysis of proportion of screen positive women who are treated pre vs post- intervention. We will use weighted least square methods appropriate for this facility-randomized three-wave step wedge design, where all clinics begin in the control condition, We will consider the intervention effect to be fixed throughout the exposed period, but random effects per facility and wave. To analyze secondary outcomes of increase in proportion of trained providers (the **REACH** outcome) and increase in number screen-positive (secondary outcome) we will use the same analysis approach for the binary and count outcome. Exploratory analysis will examine potential effect modification of facility-level factors such as patient volume, patient to provider ratio, and women screened. Potential multi-level adjustment variables include individual-level factors such as age and access to resources. The HPV sub-study in women treated with TA will assess HPV clearance in HPV-positive women. Assuming 70% of screen-positive women test positive for HPV prior to TA (N = 140), the confidence interval for HPV clearance will be +/-8.1%

- **ADOPTION**

Our primary outcomes for adoption will be

1. the proportion of clinics incorporating TA into routine care through updated policies
2. Proportion of trained providers performing SVA-SAT +TA for screen positive women and

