Working together with the clinical team at the implementing facilities, we will develop a clinic report form that supports comprehensive data collection for women receiving cervical prevention services. Research data will be extracted from these clinical records. The data on the research clinic report form will be designed to support completeness of reporting and it will reflect standard clinical care data. This form will remain in the participant records in the health facility. We will then abstract data from this record.

Data will be entered directly to a password protected tablet and uploaded to the data files at the PHRD clinical trial facility data room. The data system at the clinical trial facility are in compliance with human subject protection guidelines. There will be no name of personal identifiers abstracted from the patient clinical files.

Written informed consent will be required for (i) participants selected for HPV testing and follow up for a 6-month period to assess for HPV clearance (ii) all qualitative interviews. The informed consent process will be voluntary and without coercion. Request to participant in the study will be done within an environment that allows the prospective participant to be well informed and to understands the purpose of the study and the expected procedures involved in participation. The informed consent form will be read and explained, and those willing to consent to participate in the study will be asked to sign a paper copy of the consent form.

After obtaining informed consent, the study staff will conduct study procedures in a private area of the clinic. Eligible reproductive health clinics will be clinics that provide cervical cancer screening services, their frontline providers, clientele and managers. We will seek permission from facilities to abstract program data and individual patient demographics and medical data.

In addition, qualitative data on single visit cervical cancer screening and treatment with thermal ablation delivery process from individual and provider key informant interviews will be collected. Logs with participant identification data will be stored in a locked file cabinet and access to all electronic data will be restricted with password and encryption protection.

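### The primary outcome is stated in two ways, and the one without a time limit lets women left untreated before crossover enter the primary contrast after it

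*Protocol*

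**What the plan says.** **Split by condition.** In Aim 2, Justification for stepped wedge design, a clinic supplies control data until it starts, and "once the cluster has begun to implement the intervention, it contributes to the" intervention period. This describes clinics. It does not say whether a woman's screening date or her treatment date places her.

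**Outcome, version 1: completion.** The Outcome Variable text names the change in treatment completion rate as primary, and Table 4 marks it so. The REACH item describes the "proportion of screen-positive women who complete treatment (target = 60%) comparing pre-implementation period to intervention periods" and counts cryotherapy, LEEP or any other procedure. The Data analysis paragraph compares the proportion treated before and after. None of these sets a time limit from the positive screen.

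**Outcome, version 2: same-day ablation.** The Power and sample size paragraph defines the primary effectiveness outcome as same-day ablation among screen-positive women.

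**Control coverage.** The same paragraph reports that "20% of cervical cancer screening clients who screened positive received cryotherapy or LEEP". The Executive Summary puts the national position at "up to 70% of screen-positive women do not receive treatment".

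**Data.** Under Baseline data period, "Routine data on the proportion of women screened, screened positive, and treated for abnormal lesions will be abstracted monthly". Human Subjects Considerations adds: "There will be no name of personal identifiers abstracted from the patient clinical files". Research data nevertheless carry a coded participant ID (Protection against risk; Confidentiality).

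**The concern.** In this design every clinic waits, then receives the equipment whose absence is given as the reason for non-treatment. A pool of untreated screen-positive women therefore builds up during the control condition and becomes treatable at crossover. The longer a clinic waits, the larger the pool.

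With no time limit, treatment of such a woman after crossover counts as completion, and the plan does not say for which condition. Counted by treatment date, it raises the intervention side. Credited to her screening date, it raises the control side. Because the pool depends on wave, a calendar-period term does not remove the effect. The model also holds the intervention effect constant over the exposed period, whereas treatment of a backlog would probably come as a burst soon after crossover.

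At stake is the size of the primary estimate, in a direction that depends on a rule the Protocol leaves open. The same-day version largely escapes the problem, so which version is primary matters.

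**Working it through.** **Inputs from the Protocol.** 30 women screened per clinic per month, 5% positive, six-month waves, 20% treated before and 60% after, ICC 0.2, alpha 0.05 (taken as two-sided), ten clinics in three waves of 3 to 4, and at least six months of control data first. Assumed layout: 3, 3 and 4 clinics, four six-month periods.

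**Plan's own counts.** 30 × 6 × 0.05 = 9 screen-positives per clinic-period, as stated. 10 × 4 × 9 = 360, also as stated.

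**Plan's own power.** The plan reads "Assuming an intracluster correlation coefficient of 0.2, alpha=0.05 and 20% treatment coverage pre-intervention", and then "we will have 80% power to detect a three-fold increase to 60% treatment coverage using thermal ablation". A basic stepped-wedge weighted least squares model (random clinic effect, fixed period effects, individual variance 0.24, between-clinic variance 0.06) gives a standard error of 0.095 and power of 98.8%. About 80% appears only with a further variance component that the plan does not quantify: roughly 0.04 for facility-by-period, or roughly 0.11 for a random treatment effect. The 80% is therefore not reproduced. That is a separate matter. The biases below do not depend on it.

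**Size of the pool.** Untreated per clinic-period: 9 × 0.80 = 7.2. At crossover, by wave: 7.2, 14.4 and 21.6 per clinic. Total: 3 × 7.2 + 3 × 14.4 + 4 × 21.6 = 151.2. With the 70% national figure: 9 × 0.70 × (3 + 6 + 12) = 132.3. For comparison, intervention clinic-periods number 3 × 3 + 3 × 2 + 4 × 1 = 19, holding 19 × 9 = 171 new positives.

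**Effect on the estimate.** Let *b* be the share of the pool treated with TA after crossover. This is an assumption, because the documents give no figure. The true difference is 0.60 − 0.20 = 0.40.

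- *Credited to the control-period screen.* Control completion becomes 0.20 + 0.80*b*, so the difference is 0.40 − 0.80*b*.
- *Counted by treatment date over new positives.* In the first period after crossover the ratio for wave *k* becomes 0.60 + 0.80*kb*. Put through the weighted least squares estimator, this adds about 1.64*b*.
- *Re-screened and counted as new.* Those women join numerator and denominator in that period. A 90% treatment rate among them is assumed.

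| *b* | By screening date | By treatment date | Re-screened as new |
|---|---|---|---|
| 0 | 0.40 | 0.40 | 0.40 |
| 5% | 0.36 | 0.48 | 0.42 |
| 10% | 0.32 | 0.56 | 0.44 |
| 25% | 0.20 | 0.81 | 0.49 |

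With no true effect and *b* = 5%, counting by treatment date alone gives +0.08, close to one standard error. Under the basic model, crediting the screening date lowers power to 92% at 10% and 56% at 25%.

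**Same-day ablation.** A woman not treated on the day of her control-period screen remains a control failure whatever happens later. Bias is zero, except by the re-screening route.

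**The case against.** **Same-day ablation closes the path.** This stands for that version, and it is why the point is conditional. But the Outcome Variable text, Table 4 and the analysis paragraph all state the other version.

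**Nobody says these women return.** This also stands. Appendix 1 lists poor follow-up, poor referral and low turn-out as barriers, which argues for a low share. On the other side, the Background reports a 24-week delay between diagnosis and excision at one hospital, and the Training phase plans outreach before on-site training to supply clients for screening and TA demonstration. Later treatment is plausible, but its extent is unknown.

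**The pool is a maximum.** It is. It assumes nobody is treated later while her clinic waits. With even accrual, mean waits at crossover are about 3, 6 and 9 months, against maxima of 6, 12 and 18. The plan expects 90% to be eligible for ablation: 0.90 × 151.2 = 136. Against that, women found positive before baseline are not included.

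**The treatment-date count is not a proper proportion.** Correct: the returning women are in the numerator only. At *b* = 25% the wave 3 ratio reaches 0.60 + 0.60 = 1.20, which would be noticed. The upper figures show sensitivity and are not forecasts. The screening-date result does not have this defect.

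**Re-screening matters little.** If re-screened women were treated at the planned 60%, the proportion would not change. Bias needs a higher rate among them.

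**Repeat visits cannot be linked.** A reader might infer this from the rule against abstracting identifiers. The documents do not support it, because coded participant IDs exist. They do not say, however, that the code links repeat visits in chart abstraction.

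**A SAP could settle attribution.** It could. It would still face two stated primary outcomes, and it could not recover an earlier positive screen that was never recorded.

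**Conclusion.** The primary outcome contradicts itself within the Protocol, and the completion version is open to carry-over from the control into the intervention condition. If 5% to 25% of the untreated pool is treated after crossover, a true 0.40 becomes about 0.36 to 0.20 by screening date or 0.48 to 0.81 by treatment date. This rests on the plan's 9 positives and 20% coverage, a 3/3/4 layout over four periods, an assumed return share that is equal across waves, and, for the treatment-date count, return in the first period after crossover.

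Two stronger readings are tempting. One is that the backlog certainly distorts the result. The documents give no return share, and under same-day ablation without re-screening the bias is zero. The other is that splitting data by clinic start already fixes a biased rule. That sentence is a general description of the design and sets no rule for individual women, so the direction of any bias is open too.

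**What to change.** - Reconcile the Outcome Variable text, Table 4, and the power and analysis paragraphs to one primary definition.
- Assign each woman once, to her clinic's condition on the date of her first recorded positive screen.
- Count treatment only within one fixed analysis window, the same in both conditions. Same-day is the shortest such window. If it is longer, leave women whose window straddles crossover out of the primary analysis.
- Report treatment of women first found positive before crossover as a separate count, outside the primary numerator and denominator.
- Record screening date, treatment date and any earlier positive screen under the existing coded participant ID.

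With these rules the expected contrast returns to 0.20 versus 0.60.

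**Cost.** Protocol wording and a few abstraction fields. With a 30-day window, 9 / 6 = 1.5 women per clinic straddle crossover, about 15 of 360 (4%), and leave the primary analysis. With same-day, none do. The change affects counting only, not anyone's care.

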**Figure 3: Stepped Wedge Implementation**

***Randomization****:* Clinics will be randomly assigned to start intervention delivery at one of the three study steps, with clusters of 3-4 clinics per step; randomization of clinics to the order of intervention steps will be stratified by size and will take place at the stakeholder meeting, which will include participation of clinic personnel.

***Training phase****:* Before SVA-SAT + TA implementation, we shall train health providers in participating RH clinics on thermal ablation techniques, inclusive of refresher training on VIA/VILLI as part of single-visit-approach as per IARC guidelines.(66). The training curriculum will be adapted to address gaps identified during Aim 1. The research training team will provide in person, on-site hands-on training at each facility followed by technical support for a duration of one week. Each trainee will be assessed for proficiency, which will be determined through the observation of a preset number procedure and certified with a proficiency certificate. To create demand and provide an adequate number of clients for screening and demonstration of TA techniques, our team which has over 15 years of successful community engagement in this region, alongside RH clinic personnel will conduct outreach community activities prior to scheduled on-site training. The selected RH clinics have some of their providers trained on VIA/VILI and cryotherapy. Our team of investigators has three reproductive health experts with TA training skills ([name], [name], [name]) who will train trainer of trainers at each RH clinic. Training will be provided with engagement of the KMET cure-cancer program who will provide consultant training services for the trainer of trainers for the initial 2 clinics, thereafter, the research team, led by [name], together with the county trainer of trainers will provide on-site hands-on training. [name] (project-PI) and [name] are skilled in colposcopy, loop electrosurgical excision procedure (LEEP), cryotherapy and TA, with years of experience training health care providers in addition to providing cervical cancer clinical services, will lead HCP training. In addition to thermal ablation training, quarterly continuous medical education (CME) which will include refresher CMEs on cervical cancer prevention and refresher didactic training on VIA will be provided during implementation.

***Intensive implementation phase****:* Several activities will be conducted during this phase:

1. *Technical Assistance and supervision:* We shall provide on-going technical support with assessment of fidelity to SVA-SAT +TA implementation for 6-12 months. This support will be provided by Technical assistants (research personnel) with training and expertise in conducting SVA-SAT with thermal ablation. They will visit health facilities bi-weekly to observe, mentor and provide oversight for RH health providers as they begin implementation of SVA-SAT+TA. A standardized technical assistance report will be used to document their findings, which will detail challenges faced by RH facilities which may include access to supplies, staffing retention, and any other specific requirements identified by the providers.
2. *Data Abstraction:* Individual level programmatic data will be abstracted from client record using a pre-set data collection form and will include provider information, type of treatment procedures (TA, cryotherapy, others) provided to screen positive women and clinical care outcomes related to treatment.
3. *Support supervision visits:* Quarterly, the county reproductive health coordinator or designee will accompany technical assistants to health facilities to conduct supportive supervision. Refresher trainings will be scheduled to address proficiency gaps identified during these visits.
4. *Regularly scheduled research meetings* with technical assistants and study investigators will discuss technical assistants facility level SVA-SAT+TA implementation reports and address identified challenges. This strategy for product scale up has been successfully applied in the Partners Scale Up project, led by [name] (site PI) in 3 regions in Kenya.(54, 67) Implementation challenges will be discussed and solutions proposed.
5. *Quality assurance (QA):* Training sessions on data completion will be included to address challenges with quality of data from routine program data (e.g., incomplete, untimely data,) prior to implementation and during support supervision visits. Concerns arising from QA assessment will be reported to the regularly scheduled county and facility committee meetings and corrective action will be planned collectively.
6. *Formation of County and Facility Committees:* The county coordinator will be asked to convene a committee that will serve an advisory team at the county level, hosted by the County RH Coordinator. At the facility level, the RH team will be requested to convene an advisory sub-committee, that will work closely with the research team to provide input on project implementation processes and receive updates provided by the research team. The county and facility committees will be involved in the decision-making regarding provision of resources to support services. The research team will liaise with the committees to schedule regularly scheduled meetings.

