**Participants Information**

Health facility name:

|  | PID | Gender (F/M) | Cadre (Nurse, Clinical Officer, Medical Officer, OBGYN) | Role (Health facility manager, Frontline health care worker) |
| --- | --- | --- | --- | --- |
| 1 |  |  |  |  |
| 2 |  |  |  |  |
| 3 |  |  |  |  |
| 4 |  |  |  |  |
| 5 |  |  |  |  |

|  | **Pre-identified barriers** | **Did this barrier apply to your facility (Y/N)** | **Addressed** | | | **Implementation strategies deployed** | **Comments** |
| --- | --- | --- | --- | --- | --- | --- | --- |
|  |  |  | Yes | No | Partial |  |  |
| 1 | Unstructured Clinic flow-movement of clients back and forth between registration, service delivery points and cashier's office. |  |  |  |  |  |  |
| 2 | Shortage of trained staff on cervical cancer screening and treatment (SOPs), job aids, and CC screening and treatment guidelines |  |  |  |  |  |  |
| 3 | Lack of essential medication supplies and equipment. |  |  |  |  |  |  |
| 4 | Low participants turn-out for screening. |  |  |  |  |  |  |
| 5 | Provider knowledge gap and skills on CC screening and treatment |  |  |  |  |  |  |
| 6 | High staff turnover |  |  |  |  |  |  |
| 7 | Limited space for screening and treatment |  |  |  |  |  |  |
| 8 | Cost of screening and treatment |  |  |  |  |  |  |
| 9 | Negative attitude among healthcare providers |  |  |  |  |  |  |
| 10 | Negative attitude among clients |  |  |  |  |  |  |
| 11 | Poor documentation of CC services |  |  |  |  |  |  |
| 12 | Fragmented approach to screening and treatment. |  |  |  |  |  |  |
| 13 | Stigma among CCC (Comprehensive care clinic) clients at the MCH |  |  |  |  |  |  |
| 14 | Substandard supplies especially acetic acid. (Facilities used white vinegar bought from the stores) |  |  |  |  |  |  |
| 15 | Lack of baby minders |  |  |  |  |  |  |
| 16 | Lack of participant follow-up |  |  |  |  |  |  |
| 17 | Lack of appropriate referral systems |  |  |  |  |  |  |
| 18 | Long queues |  |  |  |  |  |  |
| 19 | Inadequate privacy (screening room used for other services, students present when services are being offered) |  |  |  |  |  |  |
| 20 | Duplication of tests (VIA positive participants sent for pap smear) |  |  |  |  |  |  |
| 21 | Lack of reporting tools |  |  |  |  |  |  |

Beyond the pre-identified barriers, were there any other barriers identified during the SV-SAT+TA implementation period and subsequently addressed successfully, partially or not addressed?" (Study staff completes the table below)

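### Data-completion training is tied to each clinic's roll-out, and the new clinic report form is not fixed to start before baseline, so a change in recording can be confounded with the intervention effect on treatment completion.

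*Protocol*

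**What the plan says.** **Outcome.** Protocol, Maintenance phase, Outcome Variable: "Our primary study outcome is change in treatment completion rate among screen-positive women, comparing pre-and post-intervention periods". Study Limitations (Data completeness) states that data come from clinic charts and that recording may be incomplete.

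**Control months.** Aim 2, Baseline data period: "Routine data on the proportion of women screened, screened positive, and treated for abnormal lesions will be abstracted monthly, by research staff". This runs for at least six months before the first wave. That paragraph mentions no data training or quality check.

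**Data-completion training.** Item 5 (Quality assurance) in the list of intensive implementation phase activities: "Training sessions on data completion will be included to address challenges with quality of data from routine program data". The sentence goes on to give examples of the problem and the timing: "e.g., incomplete, untimely data,) prior to implementation and during support supervision visits". Support supervision visits are item 3 of the same list and are quarterly.

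**Abstraction.** Item 2 of that list: "Individual level programmatic data will be abstracted from client record using a pre-set data collection form". The REACH paragraph under Outcome Variable separately says that individual-level data will be used to compare treatment completion between the pre-implementation and intervention periods.

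**Clinic report form.** Human Subjects Considerations: "Working together with the clinical team at the implementing facilities, we will develop a clinic report form that supports comprehensive data collection". The form is designed for completeness and becomes the source for abstraction. No date or phase is given.

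**Starting quality of the records.** Appendix 1 lists "Poor documentation of CC services" as pre-identified barrier 11 and missing reporting tools as barrier 21. It asks whether the deployed strategies dealt with them.

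**The concern.** A treatment counts only if it is in the record, and a screen-positive woman enters the denominator only if she is in the record. Anything that changes how completely clinics write these facts down changes the measured completion rate, even if care does not change.

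The protocol describes poor recording at the start and plans measures to improve it. One of these, the training, is attached to roll-out. The other, the form, is not dated. A stepped-wedge model adjusts for calendar time, because clinics in different conditions are compared within the same period. It does not adjust for something that switches on in each clinic together with the intervention. That component becomes part of the estimated effect.

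The primary comparison is at stake, and so is Aim 3, whose decision model takes reach and effectiveness from Aim 2. Analysis cannot repair the loss afterwards: a treatment never written down in a control month cannot be recovered.

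**Working it through.** **1. Is recording support the same in both conditions?**

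| Element | Control months | From roll-out |
| --- | --- | --- |
| Data-completion training | Only sessions before implementation; lead time not stated | Repeated at quarterly supervision visits |
| Clinic report form | Start not stated | Start not stated |
| Individual-level abstraction | Stated (REACH paragraph) | Stated (REACH paragraph; item 2) |
| Comparison of record completeness between periods | None stated | None stated |

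Training differs by condition as written. The form is open. Abstraction level is not a difference. The only related sensitivity analysis, in Study Limitations, covers concurrent interventions.

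**2. Inputs for size.** From Power and sample size: control completion 20%, target 60% (a 40-point effect), ICC 0.2, alpha 0.05 (taken as two-sided), nine screen-positive women per facility per wave. The documents give no recording rate, so every recording share below is an assumption.

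**3. Treatments under-recorded, no true effect.** Let s0 and s1 be the shares of treatments recorded before and after crossover.

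False rise = true rate × (s1 − s0)

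- True 20%, s0 = 0.80, s1 = 0.95: 0.20 × 0.15 = 3 points.
- True 40%, s0 = 0.50, s1 = 0.95: 0.40 × 0.45 = 18 points (20% recorded before, 38% after).

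**4. Same mechanism, tied to the protocol's 20% control rate.** If 20% is the recorded rate and recording is complete afterwards (s1 = 1), the true rate is 0.20 / s0 and the false rise is 0.20 / s0 − 0.20.

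| s0 | True rate | False rise | SE | Chance of a significant result favouring the intervention |
| --- | --- | --- | --- | --- |
| 0.8 | 25.0% | 5.0 points | 0.081 | 9% |
| 0.7 | 28.6% | 8.6 points | 0.083 | 18% |
| 0.5 | 40.0% | 20.0 points | 0.087 | 63% |

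The chance is Φ(rise / SE − 1.96); for s0 = 0.8, 0.050 / 0.081 − 1.96 = −1.34, which gives 9%. The SE comes from a Hussey-Hughes weighted least squares model with ten clinics (3, 3, 4), four periods and the inputs in step 2. With no bias the chance in this direction would be 2.5%.

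The same model does not reproduce the stated 80% power for 20% against 60%: it gives 0.40 / 0.087 − 1.96 = 2.64, or 99.6%. With cluster autocorrelation set to 0 it gives 82.2% to 94.2%, depending on the variance choice. The stated power is not disputed here, but the last column is only a rough guide.

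**5. Untreated women under-recorded, no true effect.** Let u be the share of untreated screen-positive women who are recorded, with all treated women recorded.

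Recorded rate = true / (true + (1 − true) × u)

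- True 20%, u = 0.5 before: 0.20 / (0.20 + 0.80 × 0.5) = 33.3%.
- u = 1 after: 20.0%. False fall: 13.3 points.
- u = 0.70 before and 0.95 after: 0.20 / 0.76 = 26.3%, then 0.20 / 0.96 = 20.8%. False fall: 5.5 points.

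The sign therefore depends on which records were missing, and the documents do not say.

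**The case against.** Four points on the other side deserve weight.

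- **Training also comes before implementation.** The first sessions therefore fall while a clinic is still contributing control data. This is right, and it rules out saying that recording improves exactly at crossover. But the lead time is not stated, and the repeated sessions at supervision visits belong to the implementation phase. The imbalance is softened, not removed.
- **Individual-level abstraction is stated for both periods.** A reader of item 2 might infer that control data are aggregate and intervention data individual. The REACH paragraph contradicts that, so this inference falls. A pre-set abstraction form also does not alter what the clinic wrote in the source record.
- **The clinic report form is undated.** A reader might infer from the reference to implementing facilities that it arrives with the intervention. The text does not say so. All ten clinics implement in the end, and the phrase is not set against control clinics. What stands is that nothing fixes the form before baseline.
- **Direction and size are unknown.** A reader might infer a bias in favour of the intervention. That assumes only treatments are missing from the records, whereas the protocol describes generally incomplete records. Step 5 shows that the opposite sign is possible. Even the 18-point case is under half of the planned 40 points.

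It can also be said that incomplete recording is already admitted as a limitation and that the SAP may add sensitivity analyses. The admission does not address a difference between conditions, and no analysis recovers events that were never recorded.

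**Conclusion.** The concern holds in a limited form. Data-completion training is linked to roll-out, control outcomes come from records that the protocol calls incomplete, and the completeness-oriented form has no fixed start. Recording of the primary outcome can therefore change around each clinic's crossover, and the planned model would count that change as intervention effect.

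The direction is open: upward if treatments were missed in control months, downward if untreated screen-positive women were. The size cannot be derived from the documents. The 3 to 18 points upward and the 5.5 to 13.3 points downward rest entirely on assumed recording shares with no true effect, and serve only to show that the bias need not be trivial. The protocol should be changed before control data collection starts.

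**What to change.** - Introduce the clinic report form and the data-completion training at all ten clinics before control data collection starts, and state the dates by clinic.
- Give the same data-quality support, including refresher sessions, in control and intervention months.
- Abstract the same individual-level fields with the same form throughout.
- Compare record completeness between control and intervention periods, for example against treatment registers, and report it with the primary result.
- If some baseline months precede the form, keep them in the primary analysis and leave them out only in a sensitivity analysis. First-wave clinics have no control data other than the baseline period, so dropping those months from the primary analysis could remove most or all of their control information.

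The cost is protocol wording, earlier delivery of a form and training that are already planned, and somewhat more data work in control months. Earlier contact with the research team slightly changes the usual-care comparator, but does so equally at every clinic.
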